5.3 Observation of Adverse Events

All adverse events will be recorded, including severity, seriousness, causal relationship, onset time, outcome, and resolution time.

5.4 Vital Signs

Blood pressure, pulse rate, respiratory rate, body temperature.

5.5 Body Weight

Body weight and BMI.

5.6 Laboratory Tests

Blood tests will be conducted twice, requiring 10 ml of blood each time.

6. Target Number of Subjects and Planned Period

6.1 Target Number of Subjects

The target number of subjects is 60:

• Study drug group (iron carboxymaltose injection): 30 cases

• Control group (extended-release ferrous sulfate tablets): 30 cases

6.2 Study Period

• Study implementation period: From the date of Ethics Committee approval until March 31, 2025 (extensions will be made as necessary).

• Patient enrollment period: From the date of Ethics Committee approval until March 31, 2023.

**Statistical protocol**

1. Purpose of the Study

To evaluate the safety and efficacy of iron carboxymaltose injection compared to oral iron supplementation for the treatment of postpartum iron deficiency anemia.

1.1 Overview of the Study Design

Design: Randomized, open-label, standard treatment-controlled, parallel-group comparative study.

Groups:

Treatment Group: Iron carboxymaltose injection

Control Group: Extended-release ferrous sulfate tablets

1.2 Primary Outcome Measure

Efficacy:

Change in Hb levels at 2 weeks after administration (2 weeks postpartum).

Calculation: Change = Value at 2 weeks after administration − Value at baseline (registration and start of treatment).

1.3 Secondary Outcome Measures

Efficacy: (1) Change in ferritin levels, Hb levels, and transferrin saturation (TSAT = serum iron ÷ TIBC × 100 (%)) at 4 weeks after administration (4 weeks postpartum).

(2) Changes in the Edinburgh Postnatal Depression Scale (EPDS) scores.

Safety: (1) Incidence and frequency of adverse events.

2. General Considerations in Statistical Analysis

2.1 Interim Analysis

No interim analysis will be conducted in this study.

2.2 Data Monitoring

Data monitoring will be performed in accordance with the procedures specified in the protocol.

2.3 Data Handling

The analysis will target fixed data after the follow-up period ends.

For values below the detection limit, half of the detection limit value will be substituted.

Definitions for change and rate of change:

Change: Measurement after intervention − Baseline measurement.

Rate of Change: (Change / Baseline measurement) × 100 (%).

If necessary, variable transformations such as square root or logarithmic transformations will be performed.

Missing data will not be considered in the analysis or secondary analysis, but sensitivity analysis (e.g., multiple imputation) will be conducted as needed to assess the stability of the results.

2.4 Significance Level and Confidence Interval

Unless otherwise specified, the significance level for hypothesis testing will be two-sided at 5%, and 95% confidence intervals will be calculated.

2.5 Adjustment for Multiplicity

Unless otherwise specified, no adjustment for multiplicity will be performed.

2.6 Common Rules for Data Processing

Calculation of days and periods:

Unless otherwise specified, the number of days will be calculated by subtracting the start date from the end date and adding 1.

Example:

Duration of medication: If the start and end of treatment occur on the same day, the duration is counted as 1 day.

Time to adverse event: If the adverse event occurs the day after the start of treatment, the duration to the first adverse event is 2 days.

Survival period: If the patient dies the day after the start of treatment, the survival period is 2 days.

Conversion of days to years, months, weeks:

1 year = 365.25 days, 1 month = 30.4375 days, 1 week = 7 days.

Display of period or occurrence relative to the start of treatment:

The start date of treatment will be counted as day 1, and the day before the start date as day -1.

When the term “each time point” is used, it refers to all time points where data is available for analysis.

Decimal Places and Rounding Rules:

Means, standard deviations, and medians will be displayed to one decimal place (rounding at the second decimal place).

Percentages will be displayed to one decimal place (e.g., 12.3%), rounding at the second decimal place.

No rounding will occur during intermediate calculations; rounding will only be applied to final results.

2.7 Confidence Intervals for Proportions of Events

Confidence intervals for the proportion of occurrences or response rates will be calculated using the exact method based on the F-distribution.

3. Analysis Population

3.1 Definition of Analysis Populations

3.1.1 Full Analysis Set (FAS)

The FAS will include all subjects enrolled in the study, randomized, and who received at least one dose of the study or control drug, and for whom Hb test results from the baseline visit can be obtained. Subjects with major protocol violations (e.g., lack of consent or enrollment outside the designated period) will be excluded.

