1.1 Primary Outcome Measure

Change in hemoglobin (Hb) levels at 2 weeks after administration (2 weeks postpartum).

• Calculation: Value at 2 weeks after administration − Value at 0 weeks on the registration and administration start date.

Rationale:

To evaluate the improvement in anemia.

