1.3 Safety Outcome Measure

Incidence of adverse events.

Rationale:

Set as a general measure to evaluate safety.

2. Study Design

• Nature of the Study: Confirmatory

• Design: Parallel-group comparison

• Randomization: Randomized

• Blinding: Open-label (non-blinded)

• Control Group: Oral iron supplement treatment group

This study is a single-center randomized controlled trial targeting 60 postpartum women with iron deficiency anemia. To test the primary hypothesis, postpartum women with iron deficiency anemia (Hb <10 g/dL and ferritin <30 ng/mL) will be randomly assigned to receive either iron carboxymaltose injection or extended-release ferrous sulfate tablets.

Blinding is not possible due to the differences in treatment schedules between the iron carboxymaltose injection and extended-release ferrous sulfate tablets. Event evaluation will be conducted by a monitoring officer in a blinded manner using centralized assessment.

To verify the study hypothesis, the participation period for individual subjects is set at 1 month postpartum, referencing previous studies on postpartum iron deficiency anemia.

3. Patient Enrollment and Allocation

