3.1 Patient Enrollment Method

The following procedure will be followed to promptly enroll patients after obtaining written consent:

(1) The principal investigator or researchers will obtain written consent from the subject and confirm eligibility.

(2) Eligible subjects will be assigned identification codes prior to study treatment initiation.

(3) Study treatment will be initiated according to allocation results.

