3.3 Allocation

• Allocation Ratio: 1:1

• Method: Stratified block randomization

• Adjustment Factors: Mode of delivery (vaginal delivery, cesarean section), severity of anemia (Hb < 8 g/dL, Hb ≥ 8 g/dL).

• Rationale for Adjustment Factors: To account for differences in blood loss during delivery and the effect of anemia treatment based on anemia severity.

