3.1.3 Safety Analysis Set

The safety analysis will include all subjects who were randomized and received at least one dose of the study or control drug, grouped by the treatment actually received.

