3.2 Correspondence with Statistical Analysis Items

Efficacy evaluations will primarily be based on the FAS. The PPS analysis will be conducted as a reference. Safety evaluations will be based on the safety analysis set.

4. Plan for Breakdown and Exposure Analysis

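### The FAS requires a first dose taken after open-label allocation, so a woman who takes neither drug leaves the primary analysis for a reason that may depend on her arm

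*Combined protocol and SAP*

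**What the plan says.** SAP 3.1.1 sets these conditions for the FAS: the woman was enrolled, was "randomized, and who received at least one dose of the study or control drug", and has a baseline Hb. It then excludes major protocol violations and gives two examples, missing consent and enrolment outside the permitted period. SAP 3.2 states that "Efficacy evaluations will primarily be based on the FAS", so this set governs the superiority ANCOVA in SAP section 6.

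Protocol section 2 describes the trial as open-label. Protocol 3.1 puts allocation before dosing: "Study treatment will be initiated according to allocation results". The safety set in SAP 3.1.3 also requires a dose, and its women are "grouped by the treatment actually received". The FAS text has no matching statement on grouping.

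**The concern.** Randomisation protects the comparison only for the women who stay in it. A condition that is met or failed after the arm is known can remove different kinds of women from the two arms. Here a woman is offered weekly infusions or daily tablets, knows which, and may then take neither. Blinded central assessment in protocol section 2 covers event evaluation, not the decision to start treatment, so it does not help.

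At stake is whether the superiority test compares women as randomised or only women who went on to take iron. With 30 per arm, one woman is 1/30 = 3.3% of her arm.

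**Working it through.** **Step 1. When is each FAS condition settled?**

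| Condition (SAP 3.1.1) | Before or after allocation |
|---|---|
| Consent; enrolment within the period | Before (protocol 3.1) |
| Baseline Hb available | In practice before: Hb is needed for eligibility (below 10 g/dL) and for the 8 g/dL stratum (protocol sections 2 and 3.3) |
| At least one dose of either drug | After, with the arm known |
| Other major violations, not listed | Open: the two named cases are only examples, and SAP 3.1.2 counts prohibited co-medication as a major violation, which can occur after allocation |

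**Step 2. Who is lost?** The dose may be of either drug. A woman who refuses infusions but takes the tablets meets the condition. Only a woman who takes neither drug fails it.

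**Step 3. Does another set recover her?** The per-protocol set is a subset of the FAS, and the safety set requires a dose. No defined set holds all randomised women. The multiple imputation in SAP 2.3 is optional and addresses missing values; nothing there brings back women whom the definition leaves out. SAP 4.1 and 4.2 would show such exclusions but not correct them.

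**Step 4. How large could the effect be?** The documents give no expected number of non-starters and no SD for Hb change, so there is no figure of the plan's to reproduce. From the documents: 30 women per arm and a two-sided 5% level. Assumed: SD 1.0 g/dL; k = 1 to 3 non-starters removed from the oral arm only; their Hb change is d = 0.5 to 1.5 g/dL lower than that of other women; no true effect.

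- Shift in the between-arm difference = k × d / 30. Smallest: 1 × 0.5 / 30 = 0.017 g/dL. Largest: 3 × 1.5 / 30 = 0.150 g/dL.
- Standard error = SD × √(1/30 + 1/(30 − k)). All kept: √(2/30) = 0.258. For k = 1: 0.260 (+0.9%). For k = 3: 0.265 (+2.7%).
- Shift in standard errors: 0.017 / 0.260 = 0.06, up to 0.150 / 0.265 = 0.57.

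**Step 5. False-positive rate.** Simulation with 200,000 trials per setting and a two-sided t-test at 5%. Each woman in either arm is a would-be non-starter at random, with probability 1/30 or 3/30. Non-starters are dropped from the oral arm only.

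| Average non-starters per arm | All kept | Oral non-starters excluded |
|---|---|---|
| 1 | about 5% | about 5.0 to 5.3% |
| 3 | about 5% | about 5.2 to 8.0% |

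The ranges cover d = 0.5 to 1.5 g/dL. Non-starter status must be random here. Forcing equal numbers into each arm pushes the all-kept rate down to 3.1 to 4.9%, which is an artefact of that set-up and would exaggerate the contrast. The t-test stands in for the planned ANCOVA.

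**The case against.** The strongest case against the point is that few women will be affected. Protocol 1.1 takes baseline as "Value at 0 weeks on the registration and administration start date", which suggests that treatment starts on the day of registration and leaves little time to withdraw. Every input to the size calculation is assumed, and with an average of one non-starter there is almost no inflation. The disposition summaries would make any exclusions visible. All of this stands, and it limits the size of the problem. It does not remove a post-allocation condition from the primary set.

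The fix also has a limit. The endpoint is timed from administration, which an undosed woman does not have, and SAP 2.3 says "Missing data will not be considered in the analysis or secondary analysis". Without a 2-week sample she drops out of the primary ANCOVA under any FAS definition. That is correct, and the fix therefore has to include the sample.

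A reader might infer three stronger points that the documents do not support:

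- That every woman who declines her allocated arm is lost. The condition accepts a dose of either drug, so one who takes the other drug stays in.
- That the first dose is the only route out after allocation. The violations exclusion is open-ended, so this cannot be established.
- That first doses go unrecorded in the oral arm. Protocol 5.1 to 5.6 list no intake item, but SAP 2.6 computes days from the start of treatment, and unsupervised first tablets are only an inference.

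On grouping, one can argue that stating as-treated grouping for the safety set alone implies as-randomised analysis elsewhere. That is a reasonable reading, but a confirmatory plan should not leave it to be inferred.

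**Conclusion.** The point holds as a weakness of definition in the primary analysis set. It is certain in the text and probably small in effect. Removal of women who take neither drug can depend on the known arm, the violations exclusion may open a second such route, and the arm in which a woman who takes the other drug is analysed is not stated.

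The largest modelled effect, about 8%, needs an average of three non-starters, a 1.5 g/dL deficit and loss from one arm only; none of these comes from the documents. Nor do the documents support a claim that the plan favours IV iron. Losing low-gaining women from the oral arm raises the oral mean and works against IV iron. Losing them from the IV arm does the reverse, as does losing high-gaining women from the oral arm. Because the direction cannot be known in advance, the sound course is to remove the condition. If every woman starts her allocated drug, the dosing and grouping changes alter nothing.

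**What to change.** In SAP 3.1.1, define the FAS as all randomised women with valid consent and a baseline Hb, analysed in the arm to which they were randomised, whether or not a dose was taken. Limit the exclusions to the two named violations (no consent, enrolment outside the period), both settled before allocation. Keep the one-dose rule for the safety set only.

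Add a sentence for women with no dose: baseline is the registration Hb, the outcome is the Hb at 2 weeks postpartum, and this sample is to be collected. If it is missing, include them in the multiple-imputation sensitivity analysis that SAP 2.3 already allows.

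The cost is one edited definition, one added sentence and one 2-week sample per non-starter. Keeping a non-starter pulls her arm toward the untreated course. This slightly dilutes the Hb difference if she is in the IV arm and could slightly widen it if she is in the oral arm.

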3.1.2 Per Protocol Set (PPS)

The PPS will include subjects from the FAS, excluding those with major violations of the protocol, such as:

Violation of inclusion/exclusion criteria

Use of prohibited concomitant medications or therapies.

3.1.3 Safety Analysis Set

The safety analysis will include all subjects who were randomized and received at least one dose of the study or control drug, grouped by the treatment actually received.

3.2 Correspondence with Statistical Analysis Items

Efficacy evaluations will primarily be based on the FAS. The PPS analysis will be conducted as a reference. Safety evaluations will be based on the safety analysis set.

4. Plan for Breakdown and Exposure Analysis

4.1 Breakdown of Subjects

The breakdown of randomized subjects will be presented.

4.2 Summary of Withdrawals or Discontinuations

A list of subjects who withdrew or discontinued will be provided.

5. Analysis Plan for Subject Background

Summary statistics of baseline characteristics will be calculated for each analysis population by group.

For categorical variables, the frequency and percentage will be shown. For continuous variables, summary statistics (sample size, mean, standard deviation, minimum, 1st quartile, median, 3rd quartile, and maximum) will be presented.

Between-group comparisons will be made using Pearson’s chi-square test for categorical variables (Fisher’s exact test if more than 20% of expected frequencies are below 5) and Student’s t-test or the Wilcoxon rank-sum test for continuous variables. A two-sided significance level of 5% will be used.

6. Analysis Plan for Primary Outcome

The primary objective of this study is to demonstrate the superiority of iron carboxymaltose injection over extended-release ferrous sulfate tablets in terms of the change in Hb levels at 2 weeks postpartum.

The primary outcome will be analyzed by comparing the mean change in Hb levels between the two groups. The null hypothesis is that the mean change in Hb for the treatment group is equal to that of the control group (mean change difference = 0), and the alternative hypothesis is that the mean change differs between the groups.

A two-sided 95% confidence interval for the mean change difference will be calculated. Covariate-adjusted ANCOVA will be used, adjusting for factors such as delivery mode (vaginal delivery or cesarean section), severity of anemia (Hb < 8 g/dL or Hb ≥ 8 g/dL), and baseline Hb levels.

7. Analysis Plan for Secondary Outcomes

To supplement the primary analysis, secondary outcomes will be analyzed without adjusting for multiplicity. A two-sided significance level of 5% and 95% confidence intervals will be calculated.

The change in ferritin, Hb, and TSAT levels at 4 weeks postpartum will be summarized by sample size, mean, standard deviation, minimum, 1st quartile, median, 3rd quartile, and maximum. Covariate-adjusted ANCOVA will be used to analyze these outcomes.

EPDS score progression will be evaluated by calculating the proportion of subjects with scores ≥ 9 at baseline and at 4 weeks postpartum. Between-group comparisons will be conducted using the chi-square test and adjusted Mantel-Haenszel test (risk difference) with covariates for delivery mode and severity of anemia.

8. Analysis Plan for Safety Outcomes

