1.2 Secondary Outcome Measures

(1) Change in ferritin levels, Hb levels, and transferrin saturation (TSAT = serum iron ÷ TIBC × 100 (%)) at 4 weeks after administration (4 weeks postpartum).

(2) Changes in the Edinburgh Postnatal Depression Scale (EPDS) scores.

Rationale:

(1) To evaluate the improvement in anemia.

(2) To examine the impact of anemia on postpartum depression.

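### The EPDS outcome is defined as change in score, but SAP 7 plans only the proportion scoring 9 or more, with no adjustment for baseline EPDS

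*Combined protocol and SAP*

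**What the plan says.** Protocol 1.2 lists as its second secondary outcome "Changes in the Edinburgh Postnatal Depression Scale (EPDS) scores", and SAP 1.3 repeats the wording. Neither gives a cut-off, a responder definition or a time point for EPDS. SAP 2.3 defines change for the whole analysis: "Change: Measurement after intervention − Baseline measurement".

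SAP 7 covers ferritin, Hb and TSAT first. Their changes at 4 weeks get full summary statistics, and "Covariate-adjusted ANCOVA will be used to analyze these outcomes". EPDS follows, handled differently: "EPDS score progression will be evaluated by calculating the proportion of subjects with scores ≥ 9 at baseline and at 4 weeks postpartum". The threshold of 9 appears only here. On the comparison, SAP 7 says "Between-group comparisons will be conducted using the chi-square test and adjusted Mantel-Haenszel test (risk difference"), "with covariates for delivery mode and severity of anemia". Baseline EPDS is not among the covariates.

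**The concern.** The outcome as named is a within-woman difference in a score. The analysis as planned is a pair of group proportions above a threshold. No mean change, no summary of the score and no model of it is planned for EPDS, although the other outcomes worded as changes get all three.

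Three things are at stake. First, EPDS is the only outcome serving the protocol's aim of looking at postpartum depression. A report that follows the SAP would omit the outcome as defined, or the score change would be analysed after the data are seen. Second, with 30 women per arm, a chance imbalance in baseline EPDS would pass into the 4-week comparison uncorrected. Third, cutting a score at a threshold discards information, so a real effect is more likely to be missed.

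**Working it through.** **Definition against analysis**

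| Item | Ferritin, Hb, TSAT | EPDS |
|---|---|---|
| Outcome as named (protocol 1.2, SAP 1.3) | Change | Change in score |
| Analysis variable (SAP 7) | Change at 4 weeks, continuous | Score of 9 or more, yes or no, at two times |
| Summary of the change | Yes | None |
| Between-arm method | ANCOVA | Chi-square; Mantel-Haenszel risk difference |
| Baseline value of the same measure named in the adjustment | Not spelled out | No |

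The primary analysis in SAP 6 does name baseline Hb as a covariate. No other section fills the EPDS gap: SAP 8.2 covers laboratory data and vital signs only. The mismatch needs no arithmetic and no assumption.

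**Size of the power loss**

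The plan has no figure to reproduce. It gives 30 per arm (protocol 6.1) and a two-sided 5% level (SAP 2.4), but no EPDS mean, SD, proportion, correlation or effect. The following are therefore assumptions:

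- true effect d of 0.5 or 0.74 SD of the 4-week score (0.74 gives about 80% power for an unadjusted comparison of means at 30 per arm);
- control proportion scoring 9 or more at 4 weeks, pc, from 10% to 50%;
- correlation r between baseline and 4-week score of 0.5, varied from 0.3 to 0.7.

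*ANCOVA on the score.* Once baseline is a covariate, modelling the change or the 4-week score gives the same treatment effect. The residual SD is √(1 − r²), and power = Φ(d / [√(1 − r²) × √(2/30)] − 1.96). With r = 0.5 the standard error is 0.866 × 0.258 = 0.2236.

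- d = 0.5: Φ(2.236 − 1.96) = Φ(0.276) = 61%
- d = 0.74: Φ(3.309 − 1.96) = Φ(1.349) = 91%

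*Chi-square on 9 or more.* The same shift on a normal scale gives the treated proportion pt = 1 − Φ(c + d), where c = Φ⁻¹(1 − pc). Power = Φ([pc − pt − 1.96 × SE₀] / SE₁), with SE₀ pooled and SE₁ unpooled. For pc = 20% and d = 0.5: pt = 9.0%, SE₀ = √(0.145 × 0.855 × 2/30) = 0.0909, SE₁ = √((0.160 + 0.082)/30) = 0.0898, so power = Φ((0.110 − 0.178)/0.0898) = 22%.

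| pc | d = 0.5: pt | Chi-square power | Share of ANCOVA's 61% | d = 0.74: pt | Chi-square power | Share of ANCOVA's 91% |
|---|---|---|---|---|---|---|
| 10% | 3.7% | 16% | 26% | 2.2% | 24% | 27% |
| 20% | 9.0% | 22% | 37% | 5.7% | 38% | 41% |
| 30% | 15.3% | 27% | 45% | 10.3% | 48% | 52% |
| 50% | 30.9% | 32% | 53% | 23.0% | 59% | 65% |

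Simulating the tests themselves (4,000 runs per setting, r = 0.5) agreed within about 3 to 4 points. ANCOVA power was 58% to 59% and 89% to 90%. Chi-square power was 14% to 33% and 23% to 59%. The shares ran from 24% (0.139/0.589) to 66% (0.593/0.901).

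Skewed scores (gamma-shaped, r = 0.5) give the same picture:

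| Assumed mean, SD | 0.5 SD effect: ANCOVA v chi-square | 0.7 SD effect: ANCOVA v chi-square |
|---|---|---|
| 6, 4 | 57% v 16% | 81% v 24% |
| 8, 4 | 58% v 26% | 84% v 41% |
| 9, 5 | 58% v 29% | 84% v 46% |
| 10, 5 | 59% v 35% | 85% v 56% |

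The correlation moves only the ANCOVA side. At d = 0.5, ANCOVA power is 53% for r = 0.3 and 77% for r = 0.7. At d = 0.74 it is 85% and 98%. Over that range the share kept runs from 20% (0.156/0.774) to 69% (0.589/0.852).

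**The case against.** A threshold analysis is legitimate in itself. SAP 7 fixes the cut-off, the times, the tests and the effect measure in advance. A proportion above a cut-off can speak to the protocol's stated interest in postpartum depression, and the SAP presents it as its reading of score progression. All of that stands. It means the sponsor could repair the mismatch from either end, but it does not remove the mismatch.

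A reader might infer three stronger things that the documents do not support.

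- *That baseline EPDS is ignored altogether.* The proportion at baseline is calculated. What is missing is baseline EPDS in the between-arm adjustment.
- *That most of the power is lost.* With no EPDS inputs in the documents, this holds only for some settings. At r = 0.5 the loss exceeds half up to a control proportion of about 30% for d = 0.5, and up to about 20% for d = 0.74. Near 50% it does not.
- *That individual women would be misclassified as improved or unchanged.* The plan has no responder or transition rule, only group proportions at two times.

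The figures also describe the unadjusted chi-square test. The power of the stratified Mantel-Haenszel analysis was not calculated. Naming two tests without saying which leads is untidy, but it is minor for a secondary outcome with no multiplicity control.

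**Conclusion.** The concern holds as a mismatch between definition and analysis, and that part is certain from the text. The size of the power loss is conditional. Under the stated assumptions with r = 0.5, the chi-square test keeps about a quarter to two thirds (roughly 26% to 66%) of the power of an ANCOVA on the score. The loss is material throughout that range, and its size turns mainly on the undocumented proportion scoring 9 or more. EPDS is a secondary outcome with no stated power target, so the Hb conclusion does not depend on it. This should be corrected, but it does not threaten the trial's main result.

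**What to change.** In SAP 7, add as the main EPDS analysis an ANCOVA of change in EPDS score at 4 weeks on treatment, baseline EPDS, delivery mode and anemia severity. Report the adjusted mean difference with its 95% CI, and summarise the change by arm as for the other change outcomes. If the scores are markedly skewed, add a rank-based or bootstrap check. Keep the proportion scoring 9 or more as supportive, using the stratified Mantel-Haenszel risk difference at 4 weeks. The chi-square test need not be dropped, provided it is labelled as secondary to these.

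If the sponsor does intend the proportion as the outcome, protocol 1.2 and SAP 1.3 must say so, with the cut-off and time point, and the 4-week comparison should account for baseline EPDS. Adding baseline status as a third two-level stratum would give 2 × 2 × 2 = 8 strata for 60 women, or 7.5 per stratum on average, so a regression adjustment may be more practical.

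The cost is SAP wording and one extra model. No new data are needed, because SAP 7 already requires the EPDS score at both times.
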